# Empagliflozin in heart failure patients with reduced ejection fraction: a randomized clinical trial (Empire HF)

**DOI:** 10.1186/s13063-019-3474-5

**Published:** 2019-06-21

**Keywords:** Heart failure, SGLT2 inhibitors, Mechanism, Mode of action, NT-proBNP, Daily activity level, Cardiac function, Metabolic endpoints, Renal endpoints, Quality of life

## Abstract

**Background:**

Data from recent cardiovascular outcome trials in patients with type 2 diabetes (T2D) suggest that sodium-glucose cotransporter 2 (SGLT2) inhibitors can prevent development of heart failure (HF) and prolong life in patients without HF. Ongoing event-driven trials are investigating whether the same effect is present in patients with well-defined HF. The mechanism behind the effect of SGLT2 inhibitors in patients with T2D and the potential effect in patients with overt HF is presently unknown.

**Methods:**

This is a randomized, double-blinded, placebo-controlled, parallel group, clinical trial including HF patients with reduced left ventricular ejection fraction (HFrEF) with an ejection fraction ≤ 40% on optimal therapy recruited from specialized HF clinics in Denmark. The primary aim is to investigate the effect of the SGLT2 inhibitor empagliflozin on N-terminal pro-brain natriuretic peptide (NT-proBNP). Secondary endpoints include cardiac biomarkers, function and hemodynamics, metabolic and renal parameters, daily activity level, and quality of life. Patients are assigned 1:1 to 90 days treatment with empagliflozin 10 mg daily or placebo. Patients with T2D are required to be on recommended doses of anti-glycemic therapy with a hemoglobin A1c (HbA1c) of 6.5–10.0% (48–86 mmol/mol). To show a between-group difference in the change of NT-proBNP of 30%, a total of 189 patients will be included.

**Discussion:**

The Empire HF trial will elucidate the effects and modes of action of empagliflozin in HFrEF patients with and without T2D and provide important mechanistic data which will complement ongoing event-driven trials.

**Trial registration:**

Clinicaltrialsregister.eu, EudraCT Number 2017-001341-27. Registered on 29 May 2017.

ClinicalTrials.gov, NCT03198585. Registered on 26 June 2017.

**Electronic supplementary material:**

The online version of this article (10.1186/s13063-019-3474-5) contains supplementary material, which is available to authorized users.

## Background

Within recent years, attention to heart failure (HF) care in patients with type 2 diabetes (T2D) has increased markedly after results from three randomized clinical trials (RCT) evaluating the effect of sodium-glucose co-transporter 2 (SGLT2) inhibitors [1–3]. In these safety trials, it was observed that three different SGLT2 inhibitors could prevent development of HF and prolong life in patients with T2D. Recently, the results have been replicated in real life [4, 5]. The mechanism behind these observations are poorly understood and while several hypotheses have been proposed, data are lacking [6–9].

In the Empagliflozin, Cardiovascular Outcomes, and Mortality in Type 2 Diabetes (EMPA-REG OUTCOME) trial, the Canagliflozin Cardiovascular Assessment Study (CANVAS) program, and the Dapagliflozin Effect on Cardiovascular Events-Thrombolysis in Myocardial Infarction 58 (DECLARE-TIMI 58) trial, 10–14% of the included patients had a reported history of HF at baseline and a significant subgroup effect was observed with a reduction in the composite endpoint of hospitalization for HF or cardiovascular death in patients treated with empagliflozin, canagliflozin, and dapagliflozin, respectively [3, 10, 11]. However, HF was neither well-defined nor described in these trials; central information such as whether the patients with reported HF had preserved (HFpEF) or reduced (HFrEF) ejection fraction is unknown. The possible beneficial effects of SGLT2 inhibitors are unknown in patients without T2D but the primary action in the kidneys – induction of glucosuria and natriuresis – have been demonstrated in individuals without T2D [12]. Proposed derived mechanisms potentially explaining the observed cardiovascular benefits of SGLT2 inhibitors include a proportionally larger reduction in the extracellular volume (ECV) than in the plasma volume (PV) [13, 14], leading to a reduced preload, left ventricular (LV) filling pressure, and LV wall stress, the latter being the primary driver for N-terminal pro-brain natriuretic peptide (NT-proBNP) production. Thereby, a net effect of decreased NT-proBNP levels, which is associated with a decreased mortality risk in HF populations, is plausible [15, 16] and a decrease of 30% in NT-proBNP has previously been shown to be clinically significant in this population [17]. Other proposed derived mechanisms of SGLT2 inhibitors supporting beneficial cardiovascular effects in HF patients include a favorable shift in glucose and fat metabolism towards increased ketone substrate use [18, 19], renoprotective effects with changes in intrarenal hemodynamics, uricosuria and reduced albuminuria [7], and direct cardiac effects with remodeling of the myocardium ultimately leading to an improvement in the ventricular systolic function [9].

To increase the understanding of the cardiovascular effects of SGLT2 inhibitors, we are evaluating the effect of the SGLT2 inhibitor empagliflozin in HFrEF patients with a left ventricular ejection fraction (LVEF) ≤ 40% on cardiac biomarkers, function and hemodynamics, metabolic and renal parameters, and daily activity level and quality of life. The results of the Empire HF trial will complement the results from ongoing event-driven trials and may provide pathophysiological insight into the effect of this new group of drugs in HFrEF patients. Here, we present the protocol for the Empire HF trial. A checklist in accordance with the Standard Protocol Items: Recommendations for Interventional Trials (SPIRIT) for the reporting of the protocol is available (Additional file 1).

## Methods

### Study hypotheses

The study hypotheses are presented in Fig. 1. The main hypothesis of the Empire HF trial is that 90 days treatment with empagliflozin 10 mg once daily compared with placebo reduces NT-proBNP in stable HFrEF patients on optimal therapy. An exploratory hypothesis is that the treatment is associated with an increase in the daily activity level and secondary hypotheses include that the treatment: reduces the amount of visceral fat, reduces insulin resistance, and increases supply of ketones to the heart (*Metabolic hypothesis*); maintains glomerular filtration rate (GFR) and reduces estimated extracellular volume (eECV), estimated plasma volume (ePV), uric acid, and urinary excretion of albumin (*Renal hypothesis*); reduces plasma concentrations of mid-region pro-peptide of adrenomedullin (MR-proADM) and high-sensitivity cardiac troponin I (hs-cTnI) (*Cardiac Biomarker hypothesis*); improves left ventricular global longitudinal strain (LV-GLS) and LVEF at rest and during pharmacological stress (*Cardiac function hypothesis*); reduces the pulmonary capillary wedge pressure (PCWP) to cardiac index (CI) ratio during sub-maximal exercise and improves LV contractile reserve (*Hemodynamic hypothesis*); improves health-related quality of life (*Quality of life hypothesis*).

**Fig. 1 Fig1:**
[figure not shown]
Empire HF hypotheses. SGLT2 sodium-glucose cotransporter 2, GFR glomerular filtration rate, eECV estimated extracellular volume, ePV estimated plasma volume, UACR urine albumin to creatinine ratio, NT-proBNP N-terminal pro-brain natriuretic peptide, MR-proADM mid-region pro-peptide of adrenomedullin, hs-cTNI high-sensitivity cardiac troponin I, LV left ventricular, KCCQ Kansas City cardiomyopathy questionnaire, EQ-5D-5 L EuroQol 5-dimension 5-level

### Primary objective

The primary objective of the study is to assess the effect of empagliflozin on NT-proBNP.

### Secondary objectives

An exploratory objective of the study is to assess the effect of empagliflozin on daily activity level. Secondary objectives include assessment of the effects on body composition, glucose metabolism, and ketones; GFR, eECV, ePV, urid acid, and urine albumin to creatinine ratio (UACR); cardiac biomarkers including MR-proADM and hs-cTnI; LV diastolic and systolic function at rest and during low-dose dobutamine infusion with echocardiography; central invasive hemodynamics at rest and during exercise; and health-related quality of life.

### Study design

Investigator-initiated, double-blinded, placebo-controlled, parallel group RCT. Two experimental sites and five recruiting sites.

### Study population

Stable outpatients with HFrEF on optimal therapy in accordance with most recent European and national guidelines [20]. It is expected that 20% of the patients have known T2D and that an additional 30% of the patients will have a diagnosis of new onset T2D or impaired glucose tolerance based on an oral glucose tolerance test (OGTT) at the randomization visit [21, 22].

### Primary endpoint

Between-group difference in the change of plasma concentrations of NT-proBNP from baseline to 90 days.

### Secondary endpoints

All the below secondary endpoints will be quantified as the between-group difference in the change of the given endpoint from baseline to 90 days. As an exploratory endpoint, the amount of daily average accelerometer units is chosen, measured by patient-worn accelerometers [23]. Secondary endpoints include: visceral fat assessed by whole-body dual-energy X-ray absorptiometry (DXA) scan [24]; ePV assessed by hematocrit and hemoglobin [25]; glucose metabolism assessed by OGTT including assessment of insulin sensitivity quantified with the Matsuda index [21]; ketone supply to the heart assessed by measuring beta-hydroxybutyrate [26, 27]; renal function assessed by measuring GFR and eECV with chromium-51 labelled ethylenediamine tetraacetic acid (^51^Cr-EDTA) clearance [28, 29]; uric acid and UACR [30, 31]; cardiac biomarkers assessed by measuring MR-proADM and hs-cTnI [32, 33]; cardiac systolic and diastolic function including LV-GLS and LVEF assessed by transthoracic echocardiography at rest and during low-dose dobutamine stress with a dosage of 20 μg/kg/min [34, 35]; cardiac hemodynamics during sub-maximal exercise assessed by right heart catheterization (RHC) including PCWP/CI index and LV contractile reserve [36]; and health-related quality of life assessed by the questionnaires Kansas City Cardiomyopathy Questionnaire (KCCQ) and EuroQol 5-dimension 5-level (EQ-5D-5 L) questionnaire [37, 38].

**Fig. 2 Fig2:**
[figure not shown]
Schedule of enrolment, interventions, and assessments in accordance with the Standard Protocol Items: Recommendations for Interventional Trials (SPIRIT). ^#^Only performed in the patients enrolled at Herlev-Gentofte Hospital. ^*^Only performed in a sub-group of the patients enrolled at Odense University Hospital. ECG electrocardiogram, OGTT oral glucose tolerance test, DXA dual-energy X-ray absorptiometry, ^51^Cr-EDTA chromium-51 labeled ethylenediamine tetra-acetic acid. AE adverse event, SAE severe adverse event, IP investigational product

### Inclusion and exclusion criteria

Inclusion and exclusion criteria are presented in Table 1. Both HF patients with and without T2D are included. Patients with known T2D will be treated in accordance with European and national guidelines and will be on recommended, stable dose(s) of anti-glycemic drug(s) for 30 days before randomization and no additional anti-glycemic drugs will be added during the study period. Patients with new onset T2D at the randomization visit will not receive additional anti-glycemic treatment during the study period. Regarding treatment for HF, patients will be on optimal, stable medical treatment in accordance with European guidelines for 30 days before randomization. If indicated, a device will be implanted before randomization in accordance with national guidelines. For implantation of a cardioverter defibrillator (ICD) and cardiac resynchronization therapy (CRT), a minimum period of 30 and 90 days will be obtained between implantation and randomization, respectively. During the study period, conventional HF therapy will only be changed if side effects are suspected.

**Table 1 Tab1:** Inclusion and exclusion criteria

Inclusion criteria	Exclusion criteria
Optimal heart failure therapy in accordance with European and national guidelines	CRT-D/−P implanted < 90 days
LVEF ≤ 0.40	Uncorrected severe valvular disease
eGFR > 30 mL/min/1.73 m^2^	Non-compliance
BMI < 45 kg/m^2^	Use of metalozone
NYHA class I–III	NYHA class IV
Age > 18 years	Age > 85 years
	Dementia
	Admission for HF < 30 days
If T2D – optimal treatment in accordance with European and national guidelines	Admission for hypoglycemia < 12 months
If T2D – stable doses of anti-glycemic treatment for 30 days	Known sustained VT
If T2D – HbA1c 6.5–10.0%	Symptomatic hypotension and systolic BP < 95 mmHg
	Unable to perform an exercise test
	Immobilization
	Pregnancy
	Participation in other medical trials
	Previous intolerance of Empagliflozin or excipients

*LVEF* left ventricular ejection fraction, *eGFR* estimated glomerular filtration rate, *BMI* body mass index, *NYHA* New York Heart Association, *T2D* type 2 diabetes, *HbA1c* hemoglobin A1c, *CRT-D/−P* cardiac resynchronization therapy with defibrillator (−D) or without defibrillator (−P), *HF* heart failure, *VT* ventricular tachycardia, *BP* blood pressure

### Schedule of enrolment, interventions, and assessments

Eligible patients will undergo the study visits presented in Fig. 2. In addition, unlimited access to telephone and email service is available and, if considered necessary, unscheduled visits during the study period through four weeks after the end-of-study visit is planned. Follow-up will be performed by investigators, sub-investigators, and study nurses educated in the specialized treatment of HF patients and who are trained in the study protocol. Important protocol modifications will be communicated to relevant parties including regulators, the ethical review board, investigators, trial participants, trial registries, and journals.

### Statistical analyses

Intention-to-treat (ITT) analyses will be applied as the primary analysis. Analysis of the primary endpoint is comparison of the between-group difference in the change of NT-proBNP from baseline to 90 days. The primary endpoint will be analyzed using analysis of covariance (ANCOVA), with treatment as a fixed factor, the baseline NT-proBNP level as a covariate and with adjustment for age, sex, history of T2D, and site of randomization. Missing data in the primary analysis will be estimated using imputation. Approximately half the patients will have either known T2D, new-onset T2D, or impaired glucose tolerance. Test for interaction between treatment, abnormal glucose tolerance, and all the specified endpoints (predefined sub-group analyses) will be performed. Log transformation will be performed if assumption of normality is not met. After log transformation, the parameter will be further tested for normality as indicated. A two-tailed *p* value ≤ 0.05 is considered statistically significant. Normally distributed variables will be presented as mean ± standard deviation (SD) and skewed distributed variables as median and interquartile range [IQR]. Comparisons between treatment and placebo group will be performed by an unpaired two sample *t-*test, Mann–Whitney test, or χ^2^ test as appropriate.

### Sample size

Primary endpoint: Based on data from a previous study, it is expected that a reduction in NT-proBNP of 30% is clinically significant [17]. To test the primary hypothesis that empagliflozin 10 mg daily compared with placebo reduces NT-proBNP with 30% (SD of 70%) with a power of 0.80 and a significance level of 0.05, a total of *N* = 172 patients in the main study is required. To allow for dropouts, the final total sample size is planned to be 189 patients.

Low dose dobutamine sub-study: To detect a clinically significant decrease in LV-GLS of 20% (SD of 30%) in patients treated with empagliflozin compared with placebo in this secondary endpoint with a power of 0.80 and a significance level of 0.05, a total of 72 patients are required. To allow for dropouts, *N* = 119 patients are planned to be enrolled at Herlev-Gentofte Hospital in this sub-study (*Cardiac function hypothesis*).

Hemodynamic sub-study: PCWP is expected to increase to 32 ± 8 mmHg and CI to 5.0 ± 1.4 L/min/m^2^ with exercise, with a PCWP/CI ratio equal to 6.4 ± 1.4. To detect a decrease of 20% in patients treated with empagliflozin compared with placebo in this secondary endpoint with a power of 0.80 and a significance level of 0.05, a total of 61 patients are required. To allow for dropouts, *N* = 70 patients are planned to be enrolled at Odense University Hospital in this sub-study (*Hemodynamic hypothesis*).

In all the other sub-studies, the sample size is a consequence of the main study on NT-proBNP and confidence intervals will be evaluated critically. Based on previous studies it is expected to observe a possible significant difference with the used sample sizes [24, 39].

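### The hemodynamic sub-study's 61 patients do not follow from the printed PCWP/CI inputs, which give 38 to 40; the ratio's SD or the variable used needs correcting

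*Protocol article*

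**What the plan says.** Under Study hypotheses, the protocol article's hemodynamic hypothesis is that treatment "reduces the pulmonary capillary wedge pressure (PCWP) to cardiac index (CI) ratio during sub-maximal exercise". Under Secondary endpoints, PCWP/CI is among the right heart catheterization measures, and every secondary endpoint is compared between groups as a change from baseline to 90 days.

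The hemodynamic paragraph under Sample size prints three mean and SD pairs. For the components: "PCWP is expected to increase to 32 ± 8 mmHg and CI to 5.0 ± 1.4". For the endpoint: "with a PCWP/CI ratio equal to 6.4 ± 1.4". The target is set as follows: "To detect a decrease of 20% in patients treated with empagliflozin compared with placebo in this secondary endpoint". At power 0.80 and alpha 0.05, the conclusion is that "a total of 61 patients are required". Enrolment is then raised to 70 at Odense University Hospital to allow for dropouts.

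Allocation is 1:1 (Assessment and randomization) and tests are two-tailed at 0.05 (Statistical analyses).

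**The concern.** The paragraph gives everything needed to recompute its result, and the result does not come out. A 20% decrease from 6.4 is 1.28, which is 0.91 of the printed SD. An effect of that size needs far fewer than 61 patients at 80% power.

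Two features suggest where the figure came from. The SD printed for the ratio, 1.4, is the same as the SD printed for cardiac index. A 20% change in cardiac index with that SD leads almost exactly to 61. So at least one element of the paragraph (the variable, the SD or the result) appears to be wrong.

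This is one of only two sub-studies given its own sample size, and it uses right heart catheterization. Readers of the PCWP/CI result will go to this paragraph to learn what difference the sub-study was designed to detect. As written, it does not tell them reliably.

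**Working it through.** **Formula.** Two-sample comparison of means, 1:1, two-sided alpha 0.05, power 0.80: total N = 4 × (1.960 + 0.842)² × (SD/difference)² = 31.4 × (SD/difference)².

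**Check of the formula on the section's other figures**
- NT-proBNP, 30% with SD 70%: 31.4 × (70/30)² = 170.9. Rounded up per arm this is 172, as stated.
- LV-GLS, 20% with SD 30%: 31.4 × (30/20)² = 70.6. Rounded up per arm this is 72, as stated.

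**The hemodynamic paragraph, each printed pair with a 20% change**

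| Variable | Difference | SD | Total, unrounded | Rounded up per arm | t-test |
|---|---|---|---|---|---|
| PCWP/CI | 1.28 | 1.4 | 37.6 | 38 | 40 |
| Cardiac index | 1.0 | 1.4 | 61.5 | 62 | 64 |
| PCWP | 6.4 | 8 | 49.1 | 50 | 52 |

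The stated 61 is not reproduced for the named endpoint. Of the printed pairs, only cardiac index comes near it.

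**Power on the printed ratio inputs.** With difference 1.28 and SD 1.4, power is 0.940 (t-test) or 0.946 (normal) with 61 patients, and 0.965 or 0.969 with 70.

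**SD at which 61 would be right.** Solving 61 = 31.4 × (SD/1.28)² gives SD = 1.78. By t-test, power at 61 reaches 80% at SD 1.75. With 70 patients the t-test limit is about 1.88.

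**Is SD 1.4 compatible with the components?** The coefficients of variation are 8/32 = 0.25 for PCWP and 1.4/5.0 = 0.28 for cardiac index. By the delta method, ratio SD ≈ 6.4 × √(0.25² + 0.28² − 2r × 0.25 × 0.28), where r is the PCWP–CI correlation. The document gives no r. SD 1.4 requires r of about 0.66. Other values of r are assumptions that show the range:

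| Assumed r | Ratio SD | N needed (normal / t-test) | Power at 61 (t-test) |
|---|---|---|---|
| 0.5 | 1.70 | 56 / 58 | about 0.82 |
| 0.3 | 2.01 | 78 / 80 | about 0.69 |
| 0 | 2.40 | 112 / 114 | about 0.54 |

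**Detectable difference at 80% power with 61 patients (t-test).** 16% of 6.4 for SD 1.4, 19% for SD 1.7, and 27% for SD 2.4.

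**The case against.** Three objections have force.

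*Cardiac index is not the only route to 61.* It gives 61.5, which becomes 62 under the per-arm rounding that reproduces the other two figures, and 64 by t-test. A ratio SD of 1.78 gives 60.7, just as close. That SD would follow from a PCWP–CI correlation of about 0.45. It would also follow from a change score: with a cross-sectional SD of 1.4 and a baseline to 90-day correlation of about 0.19, the SD of change is 1.4 × √(2 × 0.81) = 1.78. So 61 may have been computed correctly for the ratio, or for its change, and the printed 1.4 may be the slip. This stands. A reader might infer that the sub-study was certainly sized on cardiac index; that is a strong inference from the matching numbers, not something the text shows.

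*On the printed inputs the discrepancy is conservative.* A reader might infer that the claim of 80% power has no basis, or that the sub-study is underpowered. Taken at face value, 61 patients exceed 80% comfortably. The low-power figures above depend on setting aside the printed SD and assuming a correlation that the document does not state. This also stands. The opposite inference, that the sub-study is larger than needed, is no safer, because it relies on the SD that is in doubt.

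*The consequences are limited.* PCWP/CI is a secondary endpoint in a single-site sub-study, and the trial's total of 189 rests on NT-proBNP, whose calculation reproduces. Nor would a null result be uninterpretable: it can be read from its confidence interval and the observed SD.

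None of this reconciles the paragraph. Each alternative route to 61 needs an SD or a correlation that is not printed there, and the inputs that are printed give a different answer.

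**Conclusion.** The point holds as an internal arithmetic mismatch. For a 20% decrease in a PCWP/CI ratio of 6.4 with SD 1.4, at two-sided alpha 0.05 and power 0.80, the requirement is 38 to 40 patients; the stated figure is more than 50% higher. Rounding or a change between normal and t-test methods does not explain it. Either the cardiac index inputs were used in place of the ratio's, or the ratio's printed SD was carried over from cardiac index. The document does not settle which.

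The size of the problem depends on that answer. If SD 1.4 is right, power is about 94% with 61 patients and about 96% with 70. If it is wrong, the stated 80% fails at 61 once the true SD exceeds about 1.75 to 1.78, and at 70 once it exceeds about 1.88.

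This should be fixed because a stated sample size is wrong as written. It does not threaten the primary analysis.

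**What to change.** State the SD of the exercise PCWP/CI ratio, or preferably of its 90-day change since that is the endpoint compared, and give its source. It should come from patient-level ratios, not from the SD of cardiac index. Say whether 61 was computed from that SD.

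Keep the planned 70 patients. Replace the statement that 61 are required for 80% power with one of two things: the number that follows from the documented SD, or the power or detectable difference that 61 to 70 patients provide over a range of SDs, for example 1.4 to 2.4.

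The cost is one corrected paragraph. No enrolment, procedure or analysis changes. The restated power may turn out better or worse than 80%, so the correction is best made before the PCWP/CI results are interpreted.
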